**4.4. Randomisation**

A computer-generated program for the randomisation codes was developed by the study statistician, [name], Department of Clinical Psychology, Odense University Hospital. The randomisation codes are in blocks. The number of patients per block is determined by the statistician and blinded towards the investigators. Each patient receives a numbered envelope prepared by the statistician and a secretary ([name]), containing a letter stating one of the two treatment groups. The envelopes are numbered and distributed consecutively, i.e. patient 1 gets the envelope with the number 1, patient 2 the envelope with number 2 etc. The patients, who after having received oral and written information have given their written informed consent to be included in the study, receive and open the envelope with information about the group they have been randomised to. The envelopes are kept in a locked closet at the Research Unit and are handed over to the investigator upon presentation of the signed informed consent statement on the day of inclusion. As the study is blinded towards the Hamilton rater, this rater will have no access to study patient records or study CRFs, in which the treatment group (A or B) is registered.

4.5.2. Medication for non-psychiatric indications (physical illness)

This kind of medication can be used as prescribed, provided it has no significant clinical interactions with duloxetine. Medication prescribed by other doctors during the study may be used if it doesn't interact with duloxetine or any other medication the patient is taking.

4.5.3. Medication for other psychiatric indications

This includes anxiolytics (anti-anxiety drugs) and hypnotics (drugs against sleeplessness). Current treatment with hypnotics and anxiolytics can continue unchanged throughout the whole study period, with necessary dose adaptations according to recommendation and condition. An increase of anxiolytics and hypnotics is permitted throughout the whole study period. The following new treatments are permitted during the study:

- Oxazepam in daily doses of up to 45 mg for severe anxiety
- Zopiclone in daily doses of 7.5 mg for sleep disturbances

4.5.4. Medication for bipolar disorder

Patients with bipolar depression must be in treatment with a mood stabilizer such as lithium, carbamazepine, lamotrigine, or valproate according to recommendations and in recommended doses before they enter the study. Patients with bipolar disorder, who do not receive mood-stabilising treatment, can enter the study as soon as they fulfil the conditions mentioned above. These requirements, however, must not lead to keeping patients from receiving other, optimal depression treatment. It is not allowed to use antipsychotics, as these may inhibit the effect of sleep deprivation.

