Sleep-phase-advance, in which the patient goes to sleep early and is woken-up early, i.e. the patient's diurnal rhythm is "advanced" compared to the usual pattern of sleep. Several studies have shown that ”sleep-phase-advance” in itself has had an effect similar to partial or complete sleep deprivation (Voderholzer 2003, Berger 2003). In this study, sleep-phase-advance is used in a version modified according to the possibilities of a psychiatric ward and where the aim is to maintain the improvement that has been obtained by sleep deprivation.

- Trials with pindolol (β-blocker usually used to treat high blood pressure) as an addition to sleep deprivation have shown that patients treated with pindolol experienced a better antidepressant effect and fewer relapses than the control group which solely received sleep deprivation (Smeraldi et al., 1999).
- Trials with lithium (mood stabiliser) showed that this drug was able to enhance and maintain the effect of sleep deprivation (Szuba et al. 1994, Benedetti et al. 2001).

Sleep deprivation must always be followed by a night of normal sleep (recovery sleep). Patients receiving sleep deprivation are usually hospitalised, but some patients use the method at home after sleep deprivation at a hospital or clinic (Loving et al. 2002).

The risk of switching into a manic episode after sleep deprivation is of the same magnitude as for antidepressants (Colombo 1999). No excessive frequency of suicide has been seen after its use (Vovin Ria et al. 1985, Kuhs et al. 1991).

Clinical experiences with sleep deprivation show a lower effect in patients who have not responded to long-term pharmacological treatment with several antidepressants with varying mechanisms of action (refractory depressions).

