4.1.3. Medication start phase**:** week 0 (7 days)

*Groups A and B*

After the patient has signed the informed consent form, an agreement concerning overnight stay is made with an in-patient ward in one of the county's psychiatric wards. When this has been decided, the patient can be included in the study and randomised to group A or B. All patients are switched from their present antidepressant treatment to duloxetine 60 mg daily in the morning. Patients who do not receive any current pharmacological treatment will also receive duloxetine 60 mg daily. Patient data are collected by means of questionnaires and forms as shown in flowchart 1 under inclusion visit. A deviation of +/- 2 days (window) of the duration of this phase due to a possible acute shortage of beds in the in-patient ward is acceptable.

Group B

At inclusion this group is also elucidated idiographically in regard to depression symptoms.

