4.1.4. Hospitalisation phase: week 1 (7 days)

All study participants are hospitalised and meetings with the study investigators are envisaged for each working day. All patients (both groups, A and B) are hospitalised in an open in-patient ward. See Figures 1 and 2. Previously hospitalised patients can be discharged if their condition permits it. Patients admitted due to study participation will be discharged 6 days after admission unless their condition does not allow it. If the patient stays in hospital the trial will follow the usual guidelines, but the visits will take place in the in-patient ward whenever necessary.

Group A

- During hospitalisation, Group A patients go through 3 sleep deprivations, the first one on the day of admission (see Figure 2). Sleep deprivation is mainly carried out as total sleep deprivation, i.e. the patients stay awake all night. However, in some cases partial sleep deprivation may be used, in which the patient is woken up at 02.00 a.m. and has to stay awake for the remains of the night. This can be done either due to an individual patient evaluation made by the investigator or due to a wish on the part of the patient. There may be good reason for using partial sleep deprivation in case of medical diseases such as diabetes, where the blood sugar level can get out of balance, or in other diseases that may be influenced by a longer wake period. Also elderly patients expect not to be able to stay awake all night may also profit from partial sleep deprivation. Patients who experience that their first and total sleep deprivation is too demanding may also switch over to partial sleep deprivation. A combination of total and partial sleep deprivation is thus permitted.
- In the evening after each sleep deprivation the patients must go to bed at 9 p.m. at the very latest and get up at 7 a.m. the following morning (sleep-phase advance).
- The treatment with duloxetine continues unchanged, with a dose of 60 mg daily.
- The patients are informed about light treatment on the day of admission which is given for the first time the following morning and subsequently each day of the study period. The duration of light treatment is 30 minutes. The time of day of the light treatment is decided after completion of the MEQ questionnaire (see psychometrics paragraph). In addition to this, to fight tiredness, the patients take light treatment at 4 a.m. each night during the period of sleep deprivation.

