4.6.4. Exclusion criteria

- - Clinically dominant psychic or somatic anxiety corresponding to a score of 3 or more on items 10 and 11 (score range from 0 to 4) of the Hamilton Depression Scale (HAM-D17).
  - Clinically domonating suicidal ideation corresponding to a score of 3 or more (score range from 0 to 4) on item 3 of the Hamilton Depression Scale (HAM-D17), or if patient or investigator are not certain about the degree of suicidality.
  - Alcohol or drug abuse as defined in the M.I.N.I.
  - Epilepsy, as seizures can be triggered by sleep deprivation.
  - Unsafe contraception in women in the reproductive age. ½Safe contraceptive methods are: contraceptive pills, sterilisation, gestagen depot injections, subdermal hormone implantations, hormonal vaginal rings and transdermal depot patches. It is required that fertile women as a minimum use one of these methods over the total study period and two months after the end of the study.
  - Pregnant and lactating women. All women are pregnancy-tested by a urine sample test.
  - Psychotic disorder as defined in the M.I.N.I
  - Antisocial personality disorder as defined in SCID.
  - Borderline personality disorder as defined in SCID.
  - Schizotypal personality disorder as defined in SCID.
  - Clinically significant organic brain disorder or mental retardation causing incapacity.
  - Treatment with antipsychotics
  - Treatment with drugs with a well-known and significant interaction with duloxetine, e.g. isocarboxazide, thioridazine and fluoxetine. Patients in fluoxetine treatment may be included after one week's discontinuation of treatment.
  - Clinically significantly reduced kidney or liver function.
  - ECG abnormalities which may be of clinical significance in connection with the study or study medication.
  - High blood pressure not treated by medication
  - Glaucoma
  - Patients equally fulfilling the M.I.N.I. criteria for major depression and mania or hypomania and thus suffering from a mixed condition.
  - Patients who have a record that makes it doubtful that they can comply with the guidelines of the study (expected low compliance).
  - Patients who due to their medical history or physical tests during the screening procedure were found to have signs of a somatic condition requiring treatment.
  - Patients with bipolar disorder who have not been treated with a mood stabiliser for at least one month.
  - Allergy to filler components of duloxetine tablets.

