**20.2 . Sleep deprivation**

As previously mentioned, it is a well-known fact that patients responding to sleep deprivation may have a partial or total relapse to depression after the following night's sleep. The study tries to prevent this by means of light treatment, antidepressants and sleep-phase-advance. Bipolar patients are required to be in mood-stabilising treatment to prevent mood swings. The patients will be informed about this risk, both orally and in the written patient information. Over the past year, the Psychiatric Research Unit has used sleep deprivation treatment without any problems of this kind. A literature review shows that the method can be used without causing any serious problems for the patient. It is essential to inform the patients about possible side effects. At a study visit in Milano, at the Villa Turro Clinic run by [name], the study main investigator and a member of the project group could examine the use of the method. Sleep deprivation is used routinely in this clinic, and it was demonstrated that the method was easy to use, staff was interviewed, and a patient was both interviewed and observed during the night during sleep deprivation.

The Psychiatric Research Unit is member of an international group called Clinical Chronotherapeutics in Affective Disorders, who conduct research in chronobiological methods, sleep deprivation included, and communicate their knowledge about these methods by publications and oral presentations. The Psychiatric Research Unit has gained much of their knowledge through the experiences of this group.

To ensure sufficient support to the patients during the project, the patients may contact the investigator on all week days when hospitalised and on all days of the week when not hospitalised. In addition to this the investigators will be in contact with the patient's contact person in the ward and the treating physician.

For the use by the investigators, an information sheet is prepared containing relevant information about each patient such as phone numbers of the ward, names of contact persons, responsible doctor, GP, and closest relative. This sheet is filed in the patient record. The patient receives a patient card with e.g. the investigators' cell phone numbers which the patients can call at any time during working hours and other relevant information.

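### Sections 4.5.4 and 4.6.4 set different entry conditions for bipolar patients newly started on a mood stabiliser: no minimum duration in one, at least one month in the other

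*Protocol*

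**What the plan says.** Three places in the protocol deal with mood-stabiliser treatment as a condition of entry for bipolar patients.

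- Section 4.5.4 (medication for bipolar disorder) requires treatment at a recommended dosage before entry: "Patients with bipolar depression must be in treatment with a mood stabilizer such as lithium, carbamazepine, lamotrigine, or valproate according to recommendations and in recommended" (the quote stops one word short of the dosage). It then turns to patients who are not yet treated: "Patients with bipolar disorder, who do not receive mood-stabilising treatment, can enter the study as soon as they fulfil the conditions mentioned above". No length of treatment is mentioned.
- Section 4.6.4 (exclusion criteria) lists as excluded: "Patients with bipolar disorder who have not been treated with a mood stabiliser for at least one month".
- Section 20.2 (ethical considerations, sleep deprivation) gives the purpose: "Bipolar patients are required to be in mood-stabilising treatment to prevent mood swings". It gives no duration.

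The timing after entry comes from the study-phase sections. Section 4.1.3 sets a medication start phase of 7 days and accepts "A deviation of +/- 2 days (window) of the duration of this phase due to a possible acute shortage of beds in the in-patient ward". Section 4.1.4 states: "During hospitalisation, Group A patients go through 3 sleep deprivations, the first one on the day of admission".

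**The concern.** Sections 4.5.4 and 4.6.4 both govern entry of the same patients, and neither says which prevails. Section 4.5.4 does more than leave out a detail that 4.6.4 supplies. It addresses the untreated bipolar patient directly and says when that patient may enter, which reads as a sufficient condition. Section 4.6.4 then withholds entry from some of the patients so admitted.

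Two things are at stake.

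- **Safety rationale.** Section 20.2 names mood-stabilising treatment as the protection against mood swings. As written, the protocol offers two levels of that protection. The sleep-deprivation consequence concerns Group A only, but the eligibility question concerns both groups, since all patients also start duloxetine at inclusion (section 4.1.3).
- **Who counts as eligible.** Section 11 allows some patients with eligibility violations that come to light after the study to be left out of the analysis. Whether a recently treated bipolar patient is a violation at all depends on which section is read. Section 1.12 foresees that a second site may join, which adds room for different readings.

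**Working it through.** The plan states no figure on this point, so there is none to reproduce. The check is a comparison of the texts followed by a day count.

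**Comparison.** Take a bipolar patient who was untreated at referral and has now been on a mood stabiliser in a recommended dose for ten days.

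- Section 4.5.4: the patient is on treatment and at a recommended dose, so entry is allowed.
- Section 4.6.4: ten days is less than one month, so the patient is excluded.
- Section 20.2: the patient is on treatment, and no duration is asked for.

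The wording in 4.6.4 is not fully clean either. It can also be read as excluding patients who have gone without a stabiliser for a month or more. The natural reading is at least one month of treatment, and that is the reading used here.

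**Inputs for the day count.**

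- Start phase S, from inclusion to admission: 7 ± 2 days, so 5 to 9 days (section 4.1.3).
- First sleep deprivation in Group A: day of admission (section 4.1.4).
- Lead-in L required at entry under 4.6.4: one month, taken as 28 to 31 days.
- Lead-in L required at entry under 4.5.4: no duration stated. L equals t, the time needed to reach a recommended dose. The documents give no figure for t; the literal lower limit is t = 0.

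**Formula.** Minimum exposure at the first sleep deprivation = L + S.

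- Under 4.5.4 alone, t = 0: 0 + 5 = 5 to 0 + 9 = 9 days (nominally 0 + 7 = 7).
- Under 4.6.4: 28 + 5 = 33 to 31 + 9 = 40 days (nominally 28 + 7 = 35 to 31 + 7 = 38).

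Set against the one-month lead-in itself, 5 to 9 days falls short by 28 − 9 = 19 to 31 − 5 = 26 days (nominally 28 − 7 = 21 to 31 − 7 = 24).

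**Sensitivity to t.** For the same length of start phase, the gap between the two rules is 28 − t to 31 − t days.

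| Assumed t (days) | Exposure under 4.5.4 alone (days) | Gap to 4.6.4 (days) |
| --- | --- | --- |
| 0 | 5 to 9 | 28 to 31 |
| 7 | 12 to 16 | 21 to 24 |
| 14 | 19 to 23 | 14 to 17 |

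The gap narrows as t grows and closes only if reaching a recommended dose itself takes about a month. Whatever t is, section 4.5.4 guarantees no duration.

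**The case against.** The strongest reply is that the two rules can be followed together. Section 4.5.4 is permissive and sits under medication, whereas 4.6.4 is the formal exclusion list, and exclusion criteria apply cumulatively. A patient treated for a month in a recommended dose satisfies both, and no patient must be enrolled under one and refused under the other. The protocol also provides a case report form for the inclusion and exclusion criteria. Early sleep deprivation would thus require a site to overlook a listed criterion.

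Much of this stands: a site that checks every exclusion criterion would apply the one-month rule. It does not remove the conflict, because 4.5.4 tells the investigator that these particular patients may enter once treated and dosed, with no pointer to a further wait. It is also fair that 5 to 9 days is a lower limit resting on t = 0, and that the number of patients affected is unknown. Section 12 says that the number of bipolar patients cannot be foretold.

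Two stronger readings are tempting, and the documents support neither.

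- **Bias in the comparison of A with B.** Section 2.2 says: "Trials with lithium (mood stabiliser) showed that this drug was able to enhance and maintain the effect of sleep deprivation". A reader might infer that a freshly started stabiliser distorts the group contrast. Under both rules, however, the stabiliser starts before entry and so before randomisation. Recent starters fall to A or B by chance, and recent starting is a baseline characteristic. At most it could modify the effect in bipolar patients. Section 2.2 speaks only of lithium among the permitted stabilisers and says nothing about time since starting.
- **Conflict with the two-week wait in section 20.3.** A reader might set this against the one-month rule. That wait concerns vacant beds for patients who have already agreed to take part, and longer waits are allowed after assessment. It is not about stabiliser lead-in.

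**Conclusion.** The point holds as a contradiction between two stated eligibility rules. A bipolar patient recently started on a mood stabiliser is eligible under section 4.5.4 and excluded under section 4.6.4, and section 20.2, which relies on the treatment as a safeguard, does not settle the matter.

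If 4.5.4 were applied alone, minimum exposure at the first sleep deprivation in Group A would be about 5 to 9 days, against about 33 to 40 days under 4.6.4. These figures assume that no time is needed to reach a recommended dose, that a month is 28 to 31 days, and that the start phase runs 5 to 9 days. The short exposure is a possibility under a careless or literal reading of 4.5.4, not a certainty.

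The affected patients are bipolar patients not already established on a stabiliser when approached; the protocol gives no count. No sample size, endpoint definition or planned test depends on the point. It should be corrected because it touches eligibility and a stated safeguard, and because correction is cheap.

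**What to change.** Reconcile sections 4.5.4 and 4.6.4 so that one entry condition for mood-stabiliser treatment in bipolar patients appears in both, and bring section 20.2 into line. Word the exclusion criterion so that it cannot be taken to mean a month without treatment. Which condition applies, and whether it includes a minimum duration, is for the sponsor and the investigator to decide; this review does not recommend one.

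The cost is a wording amendment. Depending on the rule chosen, some bipolar patients may enter later than section 4.5.4 now suggests. Design, sample size and analysis are unaffected.

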4.5.5. Drug accountability

All drugs, used or returned, are accounted for, and a drug registration log is kept in which this is registered at each visit. Surplus medication will be disposed of by the hospital dispensary. All information about other medication the patient uses will be registered in a special medication form throughout the whole study period. The types of mood stabilizers for patients with bipolar disorders cannot be changed, but the dosage may be adjusted if necessary. Patients who according to clinical evaluation have to be switched to another medicaton, must discontinue the study (see "Critieria for exclusion from the study"). If serum monitoring (e.g. lithium or lamotrigine) is required, this will be done according to general clinical practice. During hospitalisation, the medication is administered by the nursing staff.

**4.6. Selection of patients**

4.6.1. Information about the project

All patients examined at the Psychiatric Research Unit of Frederiksborg County are from Frederiksborg County while patients examined at Hvidovre Hospital will be from those parts of Copenhagen that constitute the Hvidovre Department of Psychiatry's catchment area (Kongens Enghave, Vesterbro, Vanløse and Valby). Accordingly, the project has to be approved by the Research Ethics Committees of Frederiksborg County and the Copenhagen and Frederiksborg communities.

Hospitalised patients as well as day patients can be included in the project. The Psychiatric Research Unit in Hilleroed (Frederiksborg County) has performed clinical trials within the area of depression for tha last many years and has thus established a good cooperation with GPs and psychiatric specialists in psychiatric practices in Frederiksborg County. Furthermore, the unit has good relations to all wards of the Frederiksborg County Department of Psychiatry's local subdepartments in the region (Frederikssund, Elsinore, Hoersholm and Hilleroed). The Head of the Department of Psychiatry of the county supports the project by joining the project group and making available the necessary beds. The Psychiatric Research Unit has distributed information about the project to doctors and nurses at the Frederiksborg County Department of Psychiatry. All wards and day units are informed about the project.

To recruit possible participants to the project, all GPs, psychiatric specialist practices and local sub-departments of psychiatry (wards and day units) will receive written information about the study. The investigators will keep informed about admissions of new patients who might be suitable for and interested in participation in the study. All psychiatric wards will be contacted weekly. At Hvidovre Hospital, the investigators will keep informed about admissions of new patients who might be suitable for and interested in later participation in the study. However, to secure the best possible project start, the study will commence at the Frederiksborg County Department of Psychiatry at Hilleroed.

The study design implies that study participants must make an effort on their own, either by doing exercises or by being treated with a combination of light, sleep deprivation and maintenance of diurnal rhythm. We expect that many patients will be interested in participating in a study using new methods of treatment, but also that patients with severe depression may have trouble being in the project. This has been taken into consideration in the inclusion criteria and in the written patient information.

